#### Primary and additional analyses

The primary effectiveness analysis is the 6-month non-inferiority of the within-group difference between CG and EG for the overall health-related quality of life measured by EQ-5D-5L. Non-inferiority will be tested between the two groups at a one-sided significance of 0.05, and if the non-inferiority of the primary endpoint was achieved, superiority will be tested at a one-sided significance of 0.025.

For secondary endpoints, non-inferiority will be also tested with a 10% non-inferiority margin and a one-sided significance of 0.05. Secondary endpoints include changes from baseline of EQ-5D-5L scores in 1 and 3 months, VAS scores, time-intensity curves, pain map, EQ-VAS scores, PSQI, PGIC, CGI-I, and satisfaction with App usage. Continuous variables will be summarized using means and standard error, and categorical variables will be summarized using frequency distributions. Parametric tests (e.g., *t* test and ANOVA) will be performed with data of normal distributions. Non-parametric tests (e.g., Wilcoxon rank-sum test and Mann–Whitney test) will be performed if parametric tests are not indicated. All statistical analyses will be performed in a validated statistical software package (e.g., SAS or SPSS).

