### Statistical methods

#### Sample size

The primary comparison in this study is the difference between EG and CG in quality of life score measuring by EQ-5D-5L. The EQ-5D-5L difference is assumed to be 0.53 with a standard deviation (SD) of 0.69 based on previous studies into the effectiveness of App-based therapy for chronic pain [40]. A sample size of 82 (41 per group) is calculated by the following formula:$$n=\frac{(1+r){({Z}_{\alpha }+{Z}_{1-\beta })}^{2}{\sigma }^{2}}{r{(\left|D\right|+\Delta )}^{2}}$$

$$Z$$ is the quantile of the standard normal distribution, $$\alpha$$ is the first-class error level, $$\beta$$ is the second-class error level for the statistical test, and $$r$$ is the allocation ratio, which is 1:1 in this equal allocation trial. Here, to detect the significant difference at a significant level of 0.05 with 80% power using a two-tailed* t* test, $${Z}_{\alpha }$$ and $${Z}_{1-\beta }$$ are determined as 1.96 ($$\alpha$$ = 0.05) and 0.84 ($$\beta$$ = 0.2), respectively. $$\sigma$$ is the expected SD of the outcome, and $$\left|D\right|$$ is the expected mean difference of the two groups. The non-inferiority limit is set at 10% [10], and $$\Delta$$ is 0.053. The sample size per group is calculated with the above formula, and the given value is 22. With the assumption of a 60% “true” responding rate and a 10% possible attrition rate, the final calculation of the sample size is 41 pairs ($$N$$ = 82).

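### The sample size uses the one-sided 0.025 level but the primary non-inferiority test is set at one-sided 0.05, and the stated 80% power belongs to neither test as described

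*Protocol article*

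**What the plan says.** **Protocol article, Sample size.** The calculation is introduced as one "to detect the significant difference at a significant level of 0.05 with 80% power using a two-tailed" t test. The normal quantiles "are determined as 1.96" (labelled α = 0.05) and 0.84 (β = 0.2). The planning values are given as "The EQ-5D-5L difference is assumed to be 0.53 with a standard deviation (SD) of 0.69". The margin Δ is 0.053, and the denominator of the formula is r(|D| + Δ)². The section then states: "The sample size per group is calculated with the above formula, and the given value is 22". Allowing for a 60% response rate and 10% attrition, this becomes 41 per group, 82 in all.

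**Protocol article, Primary and additional analyses.** The primary hypothesis is non-inferiority of the change in EQ-5D-5L utility at 6 months: "Non-inferiority will be tested between the two groups at a one-sided significance of 0.05". If it is met, "superiority will be tested at a one-sided significance of 0.025".

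**The concern.** Two adjacent sections fix the level of the same confirmatory test differently. A critical value of 1.96 is a one-sided level of 0.025; a one-sided 0.05 test has a critical value of 1.645. The analysis level is therefore twice the one-sided level used for sizing. It is also looser than the level set for the superiority step that follows.

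The sample-size text has a second mismatch. Its words describe a two-tailed test of a difference, but its formula is for non-inferiority.

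Two things are at stake. The stated 80% should be the power of the test that will be done. And the threshold for the trial's main claim should be fixed before the data are seen, because some results would count as non-inferior at one level and not at the other. The stricter reading matters more here because participants and physicians are unblinded and the primary outcome is self-reported.

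**Working it through.** **Inputs (Protocol article, Sample size).** D = 0.53, SD = 0.69, Δ = 0.053, Z values 1.96 and 0.84, 1:1 allocation, 22 evaluable per group. D + Δ = 0.583 and SD² = 0.4761.

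**1. The plan's own figure.**
- n = 2 × (1.96 + 0.84)² × 0.4761 / 0.583² = 21.96, which rounds up to 22 per group.
- 22 / 0.6 / 0.9 = 40.7, which rounds up to 41 per group, N = 82.

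Both stated figures reproduce. They do so with the margin in the denominator, so this is a non-inferiority calculation at one-sided 0.025.

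**2. Power at 22 per group.** The standard error of the difference is 0.69 × √(2/22) = 0.208. Normal-approximation power is Φ(effect / 0.208 − critical value), where the effect is 0.583 for non-inferiority and 0.53 for a difference. Exact figures use the noncentral t with 42 degrees of freedom.

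| Test | Where it appears | Calculation | Normal | Exact t |
|---|---|---|---|---|
| Non-inferiority, one-sided 0.025 | Implied by the formula and 1.96; named in neither section | Φ(2.802 − 1.960) | 80.0% | 78.2% |
| Difference, two-sided 0.05 | Wording of Sample size | Φ(2.547 − 1.960) | 72.2% | 70.2% |
| Non-inferiority, one-sided 0.05 | Primary and additional analyses | Φ(2.802 − 1.645) | 87.6% | 86.7% |

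**3. Size that would give 80% for each test described** (normal approximation).
- Difference test: 2 × (1.96 + 0.842)² × 0.4761 / 0.53² = 26.6, so 27 per group.
- Non-inferiority at one-sided 0.05: 2 × (1.645 + 0.842)² × 0.4761 / 0.583² = 17.3, so 18 per group. Then 18 / 0.6 / 0.9 = 33.3, so 34 per group, N = 68.

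**4. Can the level change the verdict?** With SD 0.69, 22 per group and t quantiles on 42 degrees of freedom, the experimental-minus-control difference must exceed:
- at one-sided 0.05: −0.053 + 1.682 × 0.208 = 0.30;
- at one-sided 0.025: −0.053 + 2.018 × 0.208 = 0.37.

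An observed advantage between 0.30 and 0.37 passes in the analysis section and fails at the sizing level. On the planning assumptions the probability of this is 86.7% − 78.2% = 8.5%. For a system truly worse by exactly the margin, the false-claim rate is 5% at one level and 2.5% at the other.

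**5. Dependence on the evaluable number.** If the 82 are counted before the stimulation test period, about 22 per group remain (82 × 0.6 × 0.9 / 2 = 22.1). If 41 per group are randomised and 10% drop out, about 37 remain (41 × 0.9 = 36.9).

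| Power (normal / exact t) | 22 per group | 37 per group |
|---|---|---|
| Non-inferiority, one-sided 0.05 | 87.6% / 86.7% | 97.7% / 97.5% |
| Non-inferiority, one-sided 0.025 | 80.0% / 78.2% | 95.3% / 94.8% |
| Superiority, one-sided 0.025 | 72.2% / 70.2% | 91.0% / 90.3% |

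**The case against.** The best defence is that the analysis section governs. It declares one-sided 0.05 openly, and nothing in the document makes that level an error in itself. Sizing at 1.96 and testing at 1.645 is conservative for power. The gated sequence is also coherent: a result that is superior at one-sided 0.025 is necessarily non-inferior at one-sided 0.05, so the sequence stays within one-sided 0.05 overall. All of this stands, and it limits the point to an inconsistency.

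It also rules out three stronger readings that a reader might infer:

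- **That the trial was sized for a test of a difference.** Only the wording says so. The formula includes the margin, and 22 reproduces as a non-inferiority size.
- **That type I error is inflated.** The level is double only relative to the one behind 1.96. At the margin the planned test errs 5% of the time, as declared.
- **That the trial is underpowered because of this mismatch, or has only 70% power for superiority.** The planned non-inferiority test has more than 80% on the protocol's assumptions. The 70% applies with 22 evaluable per group, and with 37 it is about 90%. The protocol does not claim 80% for superiority as its gated second step.

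The defence does not explain why one document uses two levels for one test, or why the power it states belongs to a test it does not name.

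**Conclusion.** The two sections contradict each other on the level and sidedness of the primary test and need to be reconciled. At 22 evaluable per group the stated 80% is the power of non-inferiority at one-sided 0.025 (78% by exact t). It is about 8 to 10 percentage points too high for the difference test described, and about 7 to 8 points too low for the non-inferiority test planned. The practical risk is a primary result whose verdict depends on which section is followed, with a probability of about 8.5% on the planning assumptions.

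Every power figure here rests on an assumed true advantage of 0.53 and an SD of 0.69. With a true difference of zero, non-inferiority at this margin and one-sided 0.025 would need about 2,661 per group: 2 × (1.96 + 0.842)² × 0.4761 / 0.053². That dependence is a separate matter, but no power quoted here should be read without it.

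**What to change.** **Primary and additional analyses.** Set the non-inferiority test at one-sided 0.025: non-inferiority is shown if the lower limit of the two-sided 95% confidence interval for experimental minus control lies above −0.053. If so, superiority is claimed when the same lower limit lies above 0.

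**Sample size.** Replace the description as a two-tailed t test for a significant difference with a non-inferiority test at one-sided 0.025, and label α to match 1.96. State superiority power separately and conditionally: about 70% with 22 evaluable per group and about 90% with 37, both assuming a true advantage of 0.53.

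**Cost.** A few sentences in two sections and no extra patients: 22 per group, 41 after inflation and N = 82 all stand. The change should be made before any comparative data are analysed.

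**Alternative.** If the sponsor prefers one-sided 0.05, the contradiction can be resolved the other way. Either the sample size uses 1.645 (18 per group before inflation, N = 68 after), or N = 82 is kept and the power with 22 evaluable per group is restated as about 87%. In either case the two-tailed difference wording should go.

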#### Secondary outcomes and safety outcomes

The differences in EQ-5D-5L utility values at 1- and 3-month follow-ups compared to baseline will be included in the secondary outcomes. Other secondary outcomes include changes in pain intensity VAS, time-intensity curve, pain map, EQ-VAS score, PSQI, PGIC, CGI-I, and satisfaction with App usage. The occurrence rate of AEs and severe AEs (SAEs) will be used as safety outcomes.

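### Ten listed secondary endpoints each get a formal non-inferiority test at one-sided 0.05, with no gate from the primary, no order, no adjustment and no supportive label

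*Protocol article*

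**What the plan says.** All of this is in the protocol article; no separate analysis plan is at hand.

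- **Primary test** (Primary and additional analyses): 6-month EQ-5D-5L, with "Non-inferiority will be tested between the two groups at a one-sided significance of 0.05".
- **The only conditional step** (same section): "if the non-inferiority of the primary endpoint was achieved, superiority will be tested at a one-sided significance of 0.025". This links the primary non-inferiority test to the primary superiority test. The secondary endpoints do not appear in it.
- **Secondary tests** (same section): "For secondary endpoints, non-inferiority will be also tested with a 10% non-inferiority margin and a one-sided significance of 0.05".
- **The list** (same section): "Secondary endpoints include changes from baseline of EQ-5D-5L scores in 1 and 3 months, VAS scores, time-intensity curves, pain map", followed by EQ-VAS, PSQI, PGIC, CGI-I and App satisfaction. Secondary outcomes and safety outcomes gives the same eight measures beyond EQ-5D-5L: "Other secondary outcomes include changes in pain intensity VAS, time-intensity curve, pain map, EQ-VAS score, PSQI, PGIC, CGI-I, and satisfaction with App usage".

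Nowhere does the article rank the secondary endpoints, adjust their level, make them wait for the primary, or describe them as supportive or exploratory.

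**The concern.** The article is not silent on secondary testing. It gives every secondary endpoint a null hypothesis, a margin and a full significance level, the same level as the primary. The preceding sentence shows that the authors write a condition when they want one, and none is written here.

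Taken at its word, the rule lets the trial report non-inferiority on EQ-5D-5L at 1 or 3 months, or on sleep, global impression or satisfaction, when the 6-month primary comparison has not shown it. Participants and their physicians know the allocation (Trial design), most of these measures are self-reported, and CGI-I is rated by the physician. An isolated secondary result could therefore be given more weight than it can bear. At stake is how the secondary results may be read. The primary test and its error rate are not affected.

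**Working it through.** **The plan's own figures.** The article states no error rate for the secondary family, so there is no such figure to reproduce. Its sample size does reproduce. Under Sample size, "The EQ-5D-5L difference is assumed to be 0.53 with a standard deviation (SD) of 0.69", with Z values 1.96 and 0.84 and margin 0.053:

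n = 2 × (1.96 + 0.84)² × 0.69² / (0.53 + 0.053)² = 7.465 / 0.3399 = 21.96, so 22 per group; 22 / 0.6 / 0.9 = 40.7, so 41 per group and N = 82.

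That calculation concerns the primary comparison only and makes no allowance for further tests.

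**Step 1: count the tests.** EQ-5D-5L at 1 and 3 months gives 2. VAS, time-intensity curve, pain map, EQ-VAS, PSQI, PGIC, CGI-I and satisfaction give 8. The total is 10 at one test per endpoint, and more if the eight are tested at several visits.

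**Step 2: allow for a smaller count.** App design places the VAS slider, time-intensity curve and pain map in the daily module. Trial design and Interventions describe daily assessments as an addition for the experimental group and restrict controls to the monthly module in their follow-up months. Data collection and management points the other way, since it has all participants taught the daily assessments after implantation. The schedule figure is not shown. If controls have no follow-up data on those three measures, 10 − 3 = 7 tests remain.

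**Step 3: family-wise rate.** Inputs: one-sided level 0.05 per test (from the article), critical value 1.645, and all true differences exactly at the margin (assumption, the worst case).

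- Independent tests: 1 − 0.95^m. For m = 10 this is 0.401; for m = 7 it is 0.302.
- Common correlation ρ (assumption; the article gives none): 1 − ∫ φ(u) · Φ((1.645 − √ρ·u)/√(1−ρ))^m du.

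| ρ | 10 tests | 7 tests |
|---|---|---|
| 0 | 40.1% | 30.2% |
| 0.3 | 30.7% | 24.5% |
| 0.5 | 24.7% | 20.3% |
| 0.7 | 18.5% | 15.9% |
| 0.9 | 11.6% | 10.5% |

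**Step 4: relate to 5%.** For ten tests the ratio to 5% runs from 11.6/5 = 2.3 to 40.1/5 = 8.0. For seven tests it runs from 10.5/5 = 2.1 to 30.2/5 = 6.0.

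**Step 5: sensitivity to the level.** At one-sided 0.025 per test, ten tests would still give 14.4% at ρ = 0.5 and 22.4% if independent.

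**The case against.** **A multiplicity rule may sit elsewhere.** This is a condensed article. Handling of secondary endpoints is commonly left to the full protocol or analysis plan, and its absence here would be no finding. That would settle the matter if the article were silent. It is not: it fixes a test, a margin and a level for each endpoint. A gate or adjustment in an unseen document would change that rule, so the sentence needs attention either way.

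**Nothing is contradicted.** The article sets 5% per test and never promises 5% for the family. It names a single primary outcome and never calls the secondary endpoints confirmatory. All of this stands. A reader might infer that the plan intends ten confirmatory claims, or that a secondary success is meant to rescue a failed primary. The text does not say so; it only fails to rule it out.

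**The size depends on assumptions.** A reader might take 25% as the error rate. That value needs a common correlation near 0.5, which the article does not supply, and all true differences at the margin. The article's own planning assumption, a difference of 0.53, is far from that boundary for EQ-5D-5L. A reader might also conclude that a claim on one named endpoint carries about five times its stated error. It does not: the rate for a single named endpoint stays at its nominal 5%, and only the chance of at least one false claim in the family rises.

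**Pre-stated tests are legitimate.** A one-line label that the secondary tests are supportive and unadjusted would remove most of the harm. This is fair, and the fix below begins with that label.

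**Conclusion.** The point holds as a badly fixed rule, at moderate strength. Ten listed secondary endpoints each carry a formal non-inferiority test at one-sided 0.05 with nothing tying them to the primary, so the text permits a non-inferiority claim on any of them after a failed 6-month primary.

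With every true difference at the margin and one test per endpoint, the chance of at least one false claim is about 12% to 40% for ten tests, or about 10% to 30% for seven, over common correlations from 0.9 to 0. No single value in that range can be taken from the document. Even the lowest is about twice 5%. The error rates of the individual tests and of the primary analysis are unchanged, and no stated figure in the article is wrong on this account.

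**What to change.** Replace the sentence on secondary testing in Primary and additional analyses with wording such as: *Secondary endpoints are supportive. They will be reported as between-group differences with confidence intervals, unadjusted for multiplicity, and will not be the basis of stand-alone non-inferiority claims.*

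If the sponsor wants a formal claim on one or two secondary endpoints, name them and test them in a pre-stated fixed sequence. Start only after primary non-inferiority is met, use the primary's one-sided level, and stop at the first failure. State where the primary superiority test sits in that sequence, and label all other secondary endpoints exploratory. (Bonferroni over ten tests, 0.05/10 = 0.005 each, would also control the family but is demanding at 41 per group.)

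The cost is a few sentences, settled before the data are analysed. It needs no extra participants or data and does not affect primary power. The downside is that the sponsor gives up stand-alone non-inferiority claims on the unsequenced secondary endpoints.

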### Outcomes

#### Primary outcome

As previously stated, EQ-5D-5L is a questionnaire which measures five dimensions. It depicts different health conditions as five-digit numbers corresponding to unique utility values. The primary outcome of the PreMaSy study is the change of EQ-5D-5L utility values between CG and EG at the 6-month follow-up compared to baseline values. After passing the eligibility screening, they will be required to fill up an EQ-5Q-5L questionnaire based on their pain experience prior to enrollment, and this value will serve as the baseline. The primary outcome formula is:$$\left({\mathrm{EQ}}_{\mathrm{EG}6}-{\mathrm{EQ}}_{\mathrm{EGbase}}\right)-\left({\mathrm{EQ}}_{\mathrm{CG}6}-{\mathrm{EQ}}_{\mathrm{CGbase}}\right)$$

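### The 0.053 margin is set on a mean difference in utility change, but the general test rule allows a rank-sum test that does not test that margin

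*Protocol article*

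**What the plan says.** All references are to the protocol article.

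- **Primary outcome.** The endpoint is the "change of EQ-5D-5L utility values between CG and EG at the 6-month follow-up compared to baseline values", written out as a formula: change in the experimental group (EG) minus change in the control group (CG).
- **Sample size.** "The EQ-5D-5L difference is assumed to be 0.53 with a standard deviation (SD) of 0.69". The symbol |D| "is the expected mean difference of the two groups". The margin is 10% of that difference, 0.053, and the calculation refers to a t test.
- **Primary and additional analyses, first paragraph.** "Non-inferiority will be tested between the two groups at a one-sided significance of 0.05", followed by a superiority test if non-inferiority is shown. No test is named here.
- **Same section, second paragraph.** It opens with the secondary endpoints, including EQ-5D-5L at 1 and 3 months, and applies a 10% margin to them. General sentences on summaries, tests and software follow. Parametric tests are for normally distributed data; otherwise, "Non-parametric tests (e.g., Wilcoxon rank-sum test and Mann–Whitney test) will be performed if parametric tests are not indicated".

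**The concern.** A non-inferiority margin has meaning only on the scale on which it was set. Here that is a difference in means. A rank-sum test asks whether a randomly chosen EG patient tends to do better than a randomly chosen CG patient. This becomes a statement about the mean only if the two distributions have the same shape and differ by a shift. The article does not say how 0.053 would enter a rank test, and in its ordinary form the test does not use the margin at all.

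If the observed distribution decides which test is run, it also decides which hypothesis is tested. A minority of EG patients with poor results can pull the EG mean down by the full margin while most EG patients rank slightly above CG. The rank test then leans towards non-inferiority although the loss that the margin is meant to limit has occurred. With the opposite pattern it leans against EG. Equal shapes cannot be taken for granted, because the two arms are managed differently.

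**Working it through.** **1. The plan's own figures.** With D = 0.53, SD = 0.69, margin 0.053, Z values 1.96 and 0.84, and r = 1:

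n = 2 × (1.96 + 0.84)² × 0.69² / (0.53 + 0.053)² = 21.96, rounded up to 22 per group.

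22 / 0.6 / 0.9 = 40.7, rounded up to 41 per group, N = 82.

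Both stated figures reproduce. The inputs are a mean difference and its SD, so the trial is sized on the mean scale.

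**2. Why the hypotheses differ.** Take an assumed case with the mean difference at the margin. CG change is N(0.30, s). EG change is 80% N(0.346, s) and 20% N(-0.15, s). The EG mean is 0.8 × 0.346 + 0.2 × (-0.15) = 0.247, so the difference is -0.053. Add the margin to EG, as a margin-shifted rank test would. The quantity tested is then

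P(EG + 0.053 > CG) = 0.8 Φ(0.099 / (s√2)) + 0.2 Φ(-0.397 / (s√2)).

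- s = 0.20: 0.8 × 0.637 + 0.2 × 0.080 = 0.526
- s = 0.69: 0.8 × 0.540 + 0.2 × 0.342 = 0.501

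A rank test is centred on 0.5. At s = 0.20 it is off-centre in favour of EG although the mean loss equals the margin. At s = 0.69 the mixture is so blurred that it hardly matters.

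**3. Error rates.** Simulated false non-inferiority at 41 per arm, true mean difference -0.053, one-sided 0.05. The switching rule is assumed to be Shapiro-Wilk p < 0.05 in either arm, then the margin-shifted rank-sum test; otherwise the Welch t test. The article names no normality test and gives no shapes. Its only SD is 0.69.

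| Assumed distributions | Welch t | Shifted rank-sum | Switching rule |
|---|---|---|---|
| Normal, SD 0.69 in both arms | 0.050 | 0.049 | 0.051 |
| Left-skewed, same shape, SD 0.69 | 0.051 | 0.051 | 0.045 |
| 80/20 mixture in EG, s = 0.69 | 0.051 | 0.050 | 0.052 |
| Same mixture, s = 0.40 | 0.051 | 0.056 | 0.054 |
| Same mixture, s = 0.30 | 0.054 | 0.068 | 0.059 |
| Same mixture, s = 0.20 | 0.055 | 0.109 | 0.084 |
| CG normal, EG left-skewed, both SD 0.69 | 0.057 | 0.131 | 0.130 |
| CG left-skewed, EG normal, both SD 0.69 | 0.043 | 0.015 | 0.016 |

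Repeat runs of the switching rule gave 0.081 to about 0.09 for the mixture at s = 0.20, and up to about 0.15 for normal CG with skewed EG. With the mixture placed in CG instead (s = 0.20), they gave 0.038 to 0.039.

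Two harsher cases depart further from the stated SD. With s = 0.25 and 15% of EG dropping by 0.8, the t test gave 0.059 and the rule 0.148. With left-skewed arms of SD 0.5 (CG) and 0.9 (EG), they gave 0.069 and 0.286.

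**4. Rank-sum test without the shift.** This form ignores 0.053. At 41 per arm it declared a positive result in 0.025 (normal), 0.017 (same-shape skew) and 0.175 (unequal spread, SD 0.5 and 0.9) of trials.

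**The case against.** The strongest objection concerns reach. The sentence stands in the paragraph on secondary endpoints, several of which are ordinal or mapped outcomes for which rank tests are natural. The only test tied to the primary comparison is the t test in the sample-size section. A reader might infer that the plan expressly switches the primary test; it does not say so. What stands is narrower: the wording is general, the section covers primary and additional analyses, and its primary paragraph names no test. Even on the strict reading, the rule governs EQ-5D-5L at 1 and 3 months, where non-inferiority is tested.

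Second, a reader might infer a formal normality pre-test. None is named, and the Shapiro-Wilk trigger and the margin shift are constructions needed for the simulation. Nor does the article establish that the rule would often switch: its remark that health states map to utilities ("It depicts different health conditions as five-digit numbers corresponding to unique utility values") says nothing about the shape of a change score. In the mixture at s = 0.20 the check switched in about a third of trials.

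Third, a reader might infer that the error rate will be inflated. Inflation needs a longer lower tail or wider spread in EG, and nothing in the document predicts that. EG receives daily monitoring and triggered appointments, which are meant to shorten its lower tail; in that direction the rule is conservative.

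Finally, test details may be left to an analysis plan that is not shown. An unspecified test would be no finding. A stated rule that conflicts with the scale of the margin is one, because an analysis plan that follows it inherits the conflict.

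**Conclusion.** The point holds in limited form. The mismatch between a margin on the mean and a rank-sum test follows from the text and needs no simulation. It is certain for EQ-5D-5L at 1 and 3 months and inferred for the primary endpoint.

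The effect on false non-inferiority depends on assumed shapes and can go either way around the nominal 5%:

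- about 5% with equal shapes, or with the 80/20 mixture at the protocol's SD of 0.69;
- about 8 to 9% with that mixture at SD 0.20;
- about 13 to 15% with a normal control arm and a left-skewed experimental arm at SD 0.69;
- about 2 to 4% with the arms reversed.

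The document does not support a claim that the rule will inflate the error rate, or any single figure for it. The sample size is unaffected. The Welch t test on the mean difference stayed between 0.043 and 0.069 at 41 per arm in the scenarios examined.

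**What to change.** State that the 6-month primary non-inferiority analysis, and the EQ-5D-5L analyses at 1 and 3 months, estimate the mean difference in utility change between EG and CG whatever the distribution. Use Welch, robust or bootstrap standard errors. Baseline adjustment is preferable but is an addition to the unadjusted formula now given, so it should be stated as a choice.

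Declare non-inferiority if the lower confidence bound at the prespecified one-sided alpha lies above -0.053. With the 0.05 now stated, that is a one-sided 95% bound, the same as the lower limit of a two-sided 90% interval (1 - 2 × 0.05 = 0.90). Using a two-sided 95% interval would move the test to one-sided 0.025 without saying so. For 1 and 3 months, write the 10% margin in utility units, as -0.053 if the primary margin is meant.

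Keep rank-based tests for these endpoints as sensitivity analyses that cannot replace the main result. Name the rank test once, since for two independent groups the Wilcoxon rank-sum and Mann-Whitney tests are the same.

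The cost is wording in the protocol or analysis plan, settled before outcome data are examined. No change to N = 82 or to data collection is needed.
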